**PROTOCOL**

**Background**

Carpal tunnel syndrome (CTS) is the most common nerve entrapment of the upper extremity mainly featured by a compression of the median nerve at the carpal tunnel in the wrist. Papanicolaou et al reported a prevalence of 3.72% in the general American population (1). Women are most often affected reporting an annual incidence of 139 per 100,000 compared to 67 cases per 100,000 in males (women/men ratio 2:1) (2). The societal burden of CTS is substantial since these patients had several income lost due to pain (3).

Treatment approaches for individuals with CTS mainly include conservative or surgical procedures; however, their scientific evidence had exhibited conflicting results. For instance a recent Cochrane Review investigating the effectiveness of hand exercises concluded that there is limited and low quality evidence of the benefit for exercise and mobilisation interventions for CTS (4). Another Cochrane Review found that surgical treatment relieves symptoms significantly better than hand splinting; but more research is needed to determine whether this conclusion can be applied to people with mild symptoms and whether surgical treatment is better than steroid injection (5).

The most updated review comparing surgical versus conservative management showed that both approaches may be effective for CTS, but surgical treatment seems to be slightly superior, showing moderate effect sizes, than conservative interventions at long-term (6). In fact, Huisstede et al found that evidence supports the effectiveness of conservative interventions at short-term, but there is a lack of evidence on mid-term and long-term effects in CTS (7). Therefore, since most trials have included short-term effects of conservative treatments, high quality randomized clinical trials determining the efficacy of conservative interventions at mid-term and long-term results are needed. This assumption would be further supported by the fact that 61% of the individuals with CTS try to avoid surgery (8) and they typically prefer conservative management as first therapeutic option because of the higher rate of complications associated to surgery (6).

Before design a randomized clinical trial comparing the effectiveness of physical therapy versus surgery, we should analyze current advances in pain neurophysiology in this condition. CTS has been primarily considered a peripheral neuropathy localized at the carpal tunnel; therefore, previous studies comparing the use of physiotherapy and surgery applied localized treatments, including exercises, mainly focused to the hand (4-7). In addition, most of the studies included in previous reviews have used physical modalities different to manual therapy, such as hand splints (9,10), or laser (11). The only trial including manual therapies, particularly exercises, into a multimodal treatment approach was that one conducted by Jarvik et al (8). Interestingly, this study only found small differences between surgery and conservative management (8).

Recent evidence suggests that CTS is a complex syndrome showing sensitization of the central nervous system (12,13). In fact, these sensitization mechanisms are independent of electro-diagnostic findings and seem to play a potential relevant role in the development of chronic CTS (14). The presence of these sensitization processes would have an impact on conservative interventions, particularly manual therapies that should be applied to these patients. This hypothesis would be supported by preliminary data suggesting that manual physical therapies can modulate sensitization mechanisms by integrating neurophysiology of pain into their rationale (15,16). No study has applied manual therapy interventions with this consideration in patients with CTS. We believe that a high quality randomized clinical trial comparing the effectiveness of this physical manual therapy approach and surgery would help to improve the conservative management of CTS.

**Objective**

The aim of our randomized clinical trial is to determine if those manual therapies including desensitization maneuvers of the central nervous system would be effective for improving pain and function outcomes in women with CTS at short, medium and long-term follow-up periods.

**Hypothesis**

Our main hypothesis is that CTS subjects receiving manual therapies including desensitization maneuvers of the central nervous system would exhibit similar outcomes in function and pain than those patients receiving surgery at all follow-up periods.

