**Sample size determinations**

We determined two sample size determination based on pain and function outcomes. For pain intensity, sample size calculation was calculated to detect treatment differences of 2.0 units on pain (MCID), assuming a standard deviation of 3.0,a 2-tailed test, an alpha level (α) of 0.05 and a desired power (β) of 90%. The estimated desired sample size with pain intensity as the main outcome was calculated to be at least 50 subjects per group. A dropout rate of 15% was expected, so around 60 patients should be included in each group.

For function, sample size calculation was determined to detect between-groups treatment differences of 0.5 points (MCID) on function subscale, assuming a standard deviation of 0.7,a 2-tailed test, an alpha level (α) of 0.05 and a desired power (β) of 90%. The estimated desired sample size with function as the main outcome measure was calculated to be at least 45 subjects per group. A dropout rate of 15%-20% was expected, so around 60 patients should be included in each group.

We decided to include pain as the main outcome in this study for the following reasons: 1, pain within the median nerve-related areas is the most common symptom experienced by patients with CTS (31); 2, pain is mainly determined by the activity of peripheral nerve nociceptors and continuous nociceptive afferent bombardment from the nerve nociceptors can lead to central and peripheral sensitization mechanisms observed in these patients (32).

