**Statistical Analysis**

Statistical analysis will be done using SPSS software, version 18.0 (Chicago, IL, USA) and it will be conducted according to intention-to-treat analysis for patients in the group to which they were allocated. Baseline demographic and clinical variables will be compared between groups with independent Student t-tests and 2 test of independence. The primary evaluation will be repeated measured analyses of covariance (ANCOVA) with time as the within-subject factor and group as the between-subject factor and adjusted for baseline outcomes for evaluating between-group differences in outcomes. We will use χ2 tests to compare self-perceived improvement at 6 and 12 months in both groups. To enable comparison of effect sizes, standardized mean score differences (SMDs) will be also calculated by dividing the mean score differences between groups by the pooled standard deviation.

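### The main hypothesis is similarity to surgery, but the trial is sized and analysed as a two-sided test for a difference, with no margin or confidence-interval rule for concluding similarity

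*Protocol*

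**What the plan says.** - **Hypothesis** (Protocol): patients receiving manual therapy "would exhibit similar outcomes in function and pain than those patients receiving surgery at all follow-up periods". No size of difference is named that would still count as similar.
- **Sample size determinations**: for pain, the main outcome, "sample size calculation was calculated to detect treatment differences of 2.0 units on pain (MCID"). The other inputs are an SD of 3.0, a two-sided alpha of 0.05 and 90% power. The result: "The estimated desired sample size with pain intensity as the main outcome was calculated to be at least 50 subjects per group". Allowing for 15% dropout, enrolment rises to about 60 per group. Function is handled the same way (0.5 points, SD 0.7, 45 per group).
- **Statistical Analysis**: the primary evaluation is a repeated-measures ANCOVA, "adjusted for baseline outcomes for evaluating between-group differences in outcomes", under intention-to-treat. Standardised mean differences are also planned.
- **Blinding**: the principal clinical investigator is to be kept unaware of crossover, so crossover is foreseen.
- **Objective**: asks whether manual therapies "would be effective for improving pain and function outcomes in women with CTS", without naming the comparator.

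The MCIDs under Outcome Measures and Sample size determinations are not offered as margins. No section says how similarity would be concluded.

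**The concern.** In the planned test the null hypothesis is no difference, which is close to what the sponsor hopes to show. Rejecting it counts against the main hypothesis, and failing to reject it does not confirm that hypothesis. The Protocol offers no third route, such as an interval compared with a margin.

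If the result were nevertheless read as support, imprecision would be rewarded: dropout and noise widen the interval, and crossover under intention-to-treat tends to shrink a real difference. All of these make non-significance more likely. A clinically relevant advantage of surgery could then be reported as similar outcomes, in a trial meant to inform whether patients can avoid surgery.

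**Working it through.** **Inputs** (Sample size determinations): pain difference 2.0, SD 3.0, two-sided alpha 0.05, power 90%, 50 evaluable per group, 15% dropout.

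**1. Reproducing the stated size.** n per group = 2(z₀.₉₇₅ + z₀.₉₀)² × SD² / d² = 2(1.960 + 1.282)² × 9 / 4 = 47.3, so 48 (49 with the noncentral t). The stated 50 fits. A one-sided test at 0.05 would need 39 to 40 and does not fit. Dropout: 50 / 0.85 = 58.8, so 59, against around 60. Function gives 42 to 43 against a stated 45. The trial is therefore sized as a two-sided difference trial, and the arithmetic is sound for that purpose.

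**2. How often a real difference would be non-significant.** SE = 3.0 × √(2/50) = 0.60. Unadjusted two-sample t-test, 98 degrees of freedom:

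| True pain difference | P(non-significant) |
|---|---|
| 1.0 | 62% |
| 1.5 | 30% |
| 2.0 | 9% |

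**3. Effect of baseline adjustment.** The Protocol states no correlation. Assume a baseline correlation r between 0.3 and 0.7, so that the SE becomes 0.60 × √(1 − r²), that is 0.572 to 0.428. By the normal approximation, P(non-significant) = Φ(1.96 − d/SE). At 1.0 point this is about 58% to 35%, and at 1.5 points about 25% to 6%. The figures in step 2 are therefore at the upper end.

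**4. Interval width.** The 95% half-width is 1.96 × 0.60 = 1.18. An observed difference up to 1.18 is non-significant. From 2.0 − 1.18 = 0.82 upwards, the interval still contains the plan's own 2.0-point MCID. So an observed difference of 0.82 to 1.18 would be non-significant yet compatible with a clinically important one.

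**5. Power of tests that could support similarity.** Assumptions: true difference 0, 50 evaluable per arm, unadjusted. The margins are also assumptions, since the Protocol states none. Non-inferiority (one-sided 0.025): Φ(M/0.60 − 1.96). Equivalence: 2Φ(M/0.60 − z) − 1, with z = 1.645 for a 90% CI and 1.96 for a 95% CI.

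| Margin M | Non-inferiority | Equivalence, 90% CI | Equivalence, 95% CI |
|---|---|---|---|
| 2.0 | 91.5% | 90.9% | 83.0% |
| 1.5 | 70.5% | 60.8% | 41.1% |
| 1.0 | 38.5% | 1.7% | 0% |

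For 90% power, non-inferiority needs 48, 85 and 190 evaluable per arm at margins 2.0, 1.5 and 1.0 (57, 100 and 224 enrolled after dividing by 0.85). Equivalence with a 95% CI at margin 2.0 needs 59 evaluable (59 / 0.85 = 69.4, so 70 enrolled), against around 60 planned.

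**The case against.** **The Protocol never says that p>0.05 will be read as similarity.** This is correct. A reader might infer it because no other criterion is given, but it remains an inference. The planned standardised differences and the quoted MCIDs would let someone judge the estimates, though neither is a decision rule. What stands is the absence of any rule for concluding similarity.

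**A statistical analysis plan, not shown, might set a margin.** It might. The Hypothesis, Sample size determinations and Statistical Analysis sections of the Protocol would still pose different questions.

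**The Background does not predict small differences.** A reader might argue that the trial will miss the effect it expects, because of one earlier trial it is said that "this study only found small differences between surgery and conservative management". That sentence reports a past result and sets no expectation for this trial. The same Background also cites a review in which surgery showed moderate effect sizes at long term. The documents do not support that argument.

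**The Objective is loose wording rather than a separate defect.** Read alone, it seems to claim effectiveness that a two-arm comparison with surgery cannot show. The Background and Hypothesis make the comparator clear, so it needs only a minor alignment.

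**The miss rates are for an unadjusted test.** This also stands. The planned ANCOVA would do better, by an amount that cannot be fixed without a correlation.

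**Conclusion.** The point holds. The main hypothesis is similarity, the trial is built to detect a difference, and nothing in the Protocol connects the two. A non-significant result would not establish similarity: the chance of one is about 62% at a true 1.0-point difference and 30% at 1.5 points, given 50 evaluable per arm, SD 3.0 and no baseline adjustment.

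A reader might infer that the trial is too small. That does not follow. The stated size reproduces, and it would also serve non-inferiority at a 2.0-point margin if there is truly no difference. Nor does it follow that any similarity test comes free. Equivalence judged on a 95% CI has only 83% power at that size, and a 2.0-point margin tolerates a loss almost as large as the plan's own MCID.

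This must be fixed before the analysis, because the planned test cannot support the main hypothesis.

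**What to change.** Choose one route.

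**(a) Keep the difference trial.** Restate the Hypothesis as a question about a difference between manual therapy and surgery. Leave the sample size and the ANCOVA as they are, and state that p>0.05 will not be reported as similarity. Cost: text only, but the trial then gives up any claim of similarity.

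**(b) Make it a non-inferiority trial.** Prespecify:
- pain at one named primary time point, in place of similarity at all follow-ups;
- a justified margin no larger than 2.0 points;
- the rule that non-inferiority is concluded only if the upper 95% confidence limit of the baseline-adjusted difference (manual therapy minus surgery, higher meaning more pain) lies below the margin;
- restated power for this test;
- a per-protocol sensitivity analysis, because crossover is foreseen.

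Cost: at a 2.0-point margin, text only. Since 2.0 equals the MCID, it is an upper bound that needs its own justification. A smaller margin lowers the power to be stated to about 71% at 1.5 and 38% at 1.0, before any gain from adjustment, or calls for more patients. If equivalence is preferred, a 90% CI keeps 91% power at 2.0; a 95% CI needs about 59 evaluable per arm for 90%.

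Under either route, reword the Objective as a comparison with surgery.

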**Study Design**

A randomized parallel-group trial will be conducted according to the CONSORT statement. The protocol has been included in the database [**https://register.clinicaltrials.gov**](https://register.clinicaltrials.gov/)with the registry number NCT01789645.

**Participants**

Women diagnosed with CTS from local regional Hospitals in Madrid (Spain) will be screened for eligibility criteria. Participants will be diagnosed according to both clinical and electrophysiological findings. To be eligible, patients should exhibit all the following signs: pain/paresthesia in the median nerve distribution, increasing symptoms during the night, positive Tinel sign, and positive Phalen sign. Symptoms should have for at least 12 months. Further, the electro-diagnostic examination had to reveal deficits of sensory and motor median nerve conduction according to international guidelines of the American Association of Electrodiagnosis, the American Academy of Neurology (AAEAAN) and American Physical Medicine and Rehabilitation Academy (APMR) (17). A median nerve sensory conduction velocity <40 mm/s and a median nerve distal motor latency >4.20 ms are considered as abnormal (17). Patients will be classified according to the classification of Padua et al (18):minimal (abnormal segmental-comparative tests only), moderate (abnormal median nerve sensory velocity conduction and distal motor latency), and severe (absence of median nerve sensory response and abnormal distal motor latency) CTS.

Participants will be excluded if they exhibit any of the following criteria: 1, any sensory/motor deficit in the ulnar or radial nerves; 2, age >65 years; 3, previous surgery or steroid injections; 4, multiple diagnoses on the upper extremity (co-existing cervical radiculopathy); 5, neck, shoulder, or upper extremity trauma; 6, systemic disease causing CTS (diabetes mellitus, thyroid disease); 7, musculoskeletal medical conditions, e.g., rheumatoid arthritis or fibromyalgia; 8, pregnancy; 9, depressive symptoms (Beck Depression Inventory, BDI-II>8 points); or, 10, male gender.

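### The electrodiagnostic entry rule conflicts with the minimal severity class, and its sensory velocity cut-off of 40 mm/s cannot be right as printed

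*Protocol*

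**What the plan says.** All of the relevant text is in one paragraph of the Protocol, section Participants.

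- **Entry condition.** Besides the clinical signs, "the electro-diagnostic examination had to reveal deficits of sensory and motor median nerve conduction", with reference to international guidelines.
- **Abnormal values.** "A median nerve sensory conduction velocity <40 mm/s and a median nerve distal motor latency >4.20 ms are considered as abnormal".
- **Severity grading.** Patients are then to be graded on a published three-level scale. The lowest grade is given as "minimal (abnormal segmental-comparative tests only"). The middle grade, moderate, needs both the sensory velocity and the motor latency to be out of range. The highest grade is given as "severe (absence of median nerve sensory response and abnormal distal motor latency").

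The document does not exempt the minimal grade from the entry condition. It gives the velocity cut-off in no other unit, and it states no distance over which conduction is measured.

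**The concern.** Two things in this paragraph do not fit together.

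First, the entry condition needs a sensory and a motor deficit together. The minimal grade is defined by the word 'only': the comparative tests are abnormal and nothing else is, so sensory velocity and distal motor latency are normal. The plan lists a grade for its own patients that its own entry rule appears to exclude. Patients come from several regional hospitals. One site could follow the entry sentence and turn a minimal patient away, while another could take the grading as a sign that such a patient belongs in the trial. The spectrum of disease enrolled, and so the population to which a finding of similar outcomes would apply, would then depend on the reader.

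Second, the velocity cut-off is a decision threshold for eligibility, and the printed value is not one that a recordable nerve response could fall below. An eligibility threshold should be usable as written.

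**Working it through.** The plan offers no calculated figure to reproduce here. The check has two parts, one of logic and one of units.

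**1. Each grade against the entry rule (sensory deficit and motor deficit)**

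| Grade | Sensory finding | Motor finding | Meets the rule? |
|---|---|---|---|
| Minimal | velocity normal (comparative tests only) | latency normal | No |
| Moderate | velocity abnormal | latency abnormal | Yes |
| Severe | response absent | latency abnormal | Yes |

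The motor column decides the matter. The only motor criterion in the paragraph is a distal latency above 4.20 ms, and a patient with abnormal comparative tests alone does not have that. Even if an abnormal comparative test were counted as a sensory deficit, the motor half of the rule would still fail on the criteria given.

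**2. The velocity cut-off against the latency cut-off**

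Inputs from the Protocol, section Participants: velocity limit 40 mm/s as printed; latency limit 4.20 ms. Assumption: a conduction distance of 60 to 140 mm, because the document gives none.

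- Distance covered in 4.20 ms at the printed velocity: 40 mm/s × 0.0042 s = 0.168 mm. This needs no assumed distance.
- Travel time at 40 mm/s = distance / velocity: 60 / 40 = 1.5 s; 140 / 40 = 3.5 s.
- Ratio to the latency limit: 1,500 ms / 4.20 ms = 357; 3,500 ms / 4.20 ms = 833.
- Velocity implied by 4.20 ms over the same distances: 60 mm / 4.20 ms = 14.3 m/s; 140 mm / 4.20 ms = 33.3 m/s.
- Travel time if the unit is read as m/s: 60 mm / 40 m/s = 1.5 ms; 140 mm / 40 m/s = 3.5 ms.

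Read as m/s, the two limits are of the same order. Read as mm/s, they differ several hundredfold at every distance in the range. A slip of a factor of 1,000 in the unit is the evident explanation.

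**3. What the printed value would do if applied literally**

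No recordable sensory response would be slower than 40 mm/s, so no patient with such a response would count as abnormal on velocity. The minimal and moderate grades would both be empty. Patients with an absent sensory response have a sensory deficit without any velocity being measured, so the severe grade would still qualify.

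Correcting the unit brings the moderate grade back. It does not settle the conflict over the minimal grade, which is a separate point.

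**The case against.** The best defence has four parts.

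- **The grading is a description and not a second entry rule.** The entry sentence is worded as a requirement. The grading only labels patients on a published scale, and a scale level with no members is harmless. Leaving it empty is simply following the protocol. This is fair as far as it goes: nothing says that minimal patients will be enrolled. But the sentence says the trial's own patients will be graded this way and lists minimal first, without noting that the level cannot occur. A site is entitled to ask which sentence governs.
- **The two cut-offs may not be the only ways to show a deficit.** The entry sentence points to outside guidelines, which may recognise other findings. That cannot be checked from the document, so the conflict is the natural reading and not a proven one. Within the document, however, no motor criterion other than latency is offered.
- **The unit is a misprint that no laboratory would follow.** Probably so, and no harm in use is shown. It is still an eligibility threshold and should be right.
- **The comparison sets a sensory velocity beside a motor latency over an assumed distance.** True. It serves only as a check on order of magnitude, and the conclusion is the same across the whole range.

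Two stronger readings are tempting and are not supported. A reader might infer that the literal velocity rule leaves nobody eligible; the definition of the severe grade contradicts that. A reader might also tie the minimal grade to the Background remark that "more research is needed to determine whether this conclusion can be applied to people with mild symptoms". That remark reports a review of surgery against splinting and concerns symptoms, whereas the minimal grade is electrophysiological. The Background itself describes sensitization as independent of electrodiagnostic findings. The gap that the protocol sets out to fill is mid-term and long-term efficacy.

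**Conclusion.** The point stands in two parts. On the natural reading, the entry rule excludes the minimal grade that the same paragraph says will be assigned, so eligibility of those patients, and the population the result covers, is unclear. The printed velocity cut-off is incompatible with the latency limit beside it, by a factor of about 360 to 830 over an assumed 60 to 140 mm. Literally applied, it would restrict entry to patients with no sensory response.

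The first part assumes that the stated velocity and latency values define the required deficits. The second assumes the distance range, though not the conclusion that the value is wrong.

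The practical weight is moderate. Severity grade is not used in the allocation, the sample size, the primary analysis or the planned genetic analysis, so no computed figure changes. What is affected is who may enter and how the result can be generalised. Eligibility belongs in the protocol, so this is not a detail to leave to a statistical analysis plan.

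**What to change.** - Check the sensory velocity cut-off and its unit against the guideline that the protocol cites, and correct the printed value. The unit appears to be m/s, but the source should settle it.
- Reconcile the entry sentence with the grading. Either remove the minimal grade and state that the conclusion is limited to moderate and severe disease, or state in the entry rule that minimal patients are eligible and on which findings. Which of the two is intended is for the sponsor and investigators to decide; the document must say one thing.
- Apply the one version at all hospitals, and compare the screening log with it so that any patient admitted or refused under the other reading is identified.

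The cost is protocol wording and a check of the screening log. No extra patients, visits or procedures are needed, and the sample size and analysis stay as they are.

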**Allocation**

Patients will be randomly assigned to receive either physiotherapy or a surgical procedure. Concealed allocation is conducted using a computer-generated randomized table of numbers created prior to the start of the data collection by a clinical researcher not involved in the recruitment and/or treatment of patients. Individual and sequentially numbered index cards with the random assignment have been prepared. The index cards will be folded and placed in sealed opaque envelopes. A second researcher will open the envelope and proceed with treatment according to the group assignment. We will blind clinicians who obtain follow-up information to patient allocation.

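### Electrodiagnostic severity is classified at entry but has no stated role in the allocation or the primary ANCOVA; pre-specifying it as a model factor is a small, nearly free improvement

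*Protocol*

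**What the plan says.** - **Protocol, Participants.** Every woman receives an electrodiagnostic grade: "Patients will be classified according to the classification of Padua et al". The three grades are minimal, moderate and severe. The same section sets an entry condition that "the electro-diagnostic examination had to reveal deficits of sensory and motor median nerve conduction".
- **Protocol, Allocation.** "Concealed allocation is conducted using a computer-generated randomized table of numbers created prior to the start of the data collection". No strata, blocks or minimisation factors are named, and the section reports that the allocation cards already exist.
- **Protocol, Statistical Analysis.** The primary evaluation is "repeated measured analyses of covariance (ANCOVA) with time as the within-subject factor and group as the between-subject factor", "adjusted for baseline outcomes for evaluating between-group differences in outcomes". No other covariate is named. The section also plans that "Baseline demographic and clinical variables will be compared between groups with independent Student t-tests", with a test of independence for categorical variables, but gives no consequence if the arms differ.
- **Protocol, Pre planned Secondary Analysis.** The one analysis listed is by COMT genotype. It does not involve the severity class.

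**The concern.** A prognostic baseline factor that is recorded on everyone, but used neither in forming the arms nor in comparing them, leaves some avoidable error in the estimate. In a trial of this size, an allocation with no stated stratification can leave the arms with noticeably different shares of severe cases. If severity predicts follow-up pain beyond what baseline pain already tells us, the estimate in that particular trial moves by the gap times the severity effect, and the residual variance is larger than it needs to be.

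There is also a practical issue. The arms are to be compared at baseline by significance tests with no stated consequence. If severity turns out to be unbalanced, the choice to adjust would then be made after seeing the data. Naming the factor in advance removes that choice.

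**Working it through.** **Inputs from the Protocol (Sample size determinations).** Pain difference 2.0, SD 3.0, two-sided alpha 0.05, power 90%, 50 per group, 15% dropout, about 60 enrolled per group.

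**Inputs assumed.** The Protocol gives neither the share of women in a class nor the effect of class on follow-up pain. For the imbalance I take a share of 20-40%, with a residual effect of 1-2 NPRS points after baseline adjustment. For the precision gain I widen this to a share of 30-50% and an effect of 0.5-2 points.

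**1. The plan's own figure.** n = 2 x (1.960 + 1.282)^2 x 3.0^2 / 2.0^2 = 47.3, so 48 per group (49 with the t distribution). The stated 50 is consistent. 50 / 0.85 = 58.8, so 59, and the stated figure of about 60 is consistent.

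**2. Chance imbalance at 60 per arm.** Let X1 and X2 be independent Binomial(60, p) counts of women in the class. The SD of the difference in shares is sqrt(2p(1-p)/60). A 10-point gap is 6 women and a 15-point gap is 9 women. Exact probabilities:

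| Class share p | SD of gap | P(gap >= 10 points) | P(gap >= 15 points) |
|---|---|---|---|
| 0.20 | 0.073 | 0.208 | 0.052 |
| 0.30 | 0.084 | 0.273 | 0.090 |
| 0.40 | 0.089 | 0.305 | 0.113 |

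This gives about 21-30% and about 5-11%. Among 50 per arm the figures are slightly higher, at about 26-36% and 6-13%.

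**3. Shift in the pain difference.** Shift = gap x residual class effect.
- Low end: 0.10 x 1 = 0.10 points.
- High end: 0.15 x 2 = 0.30 points.

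**4. Scale.** With SD 3.0 and 50 per group, the standard error of the difference is 3.0 x sqrt(2/50) = 0.60. The high-end shift is 0.30 / 0.60 = half a standard error, and 0.30 / 2.0 = 15% of the planned difference. The planning SD takes no credit for baseline adjustment, so the true standard error may be somewhat below 0.60.

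**5. Error rate.** I used a simulation of 40,000 trials with 50 per arm, class share 40%, class effect 1 point and no severity adjustment. It gives a type I error of 5.1% overall, and 5.8% among trials with a gap of 15 points or more.

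**6. What adjustment gains.** The share of variance explained by a two-level class is R2 = p(1-p)e^2 / 3.0^2.
- p = 0.3, e = 0.5: 0.21 x 0.25 / 9 = 0.006.
- p = 0.5, e = 2: 0.25 x 4 / 9 = 0.111.

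Replacing 3.0 by 3.0 x sqrt(1 - R2), the required n falls from 48 to between 48 and 43 per group. Power at 50 per group rises from 91.5% to between 91.7% and 94.2%.

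**7. Which classes can occur.** The entry condition requires both sensory and motor deficits. The least severe grade is defined as "minimal (abnormal segmental-comparative tests only". Read literally, a woman in that grade could not enter, which leaves moderate and severe. The two statements need to be reconciled. The calculation above needs only two classes.

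**The case against.** **Baseline outcome adjustment already does much of this.** It removes the part of a severity imbalance that shows in baseline pain or function. That stands, and it is why the effect in the working is a residual one. Whether much is left cannot be settled from the Protocol.

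**Chance imbalance is not bias.** This stands. Averaged over randomisations the estimate is unbiased and the test holds its level (5.1% simulated). The cost is precision, and error conditional on the imbalance that happens to occur.

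**Covariates are often left to a statistical analysis plan.** This is true in general, and a plan not shown here may add the class. However, this Protocol does state its primary model and what that model adjusts for, so a suggestion to extend that list is in scope. Simple randomisation and adjustment for the baseline outcome alone are legitimate choices. The point is an improvement to them.

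**The background does not make severity an effect modifier.** A reader might infer that it does from the remark that "more research is needed to determine whether this conclusion can be applied to people with mild symptoms". That remark concerns symptom severity in surgery versus splinting. It does not concern the electrodiagnostic class in this comparison. The Background also holds that sensitization, which the manual therapy targets, does not depend on nerve-conduction results. The document therefore does not support a claim that the contrast depends on this class.

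**The class is not wholly unused.** It may fall under the planned baseline comparisons. This is fair, but those comparisons do not enter the treatment estimate.

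**Conclusion.** The point holds as a minor design improvement. The severity class is recorded for every woman and has no stated role in the allocation or in the primary comparison. Under the assumed class share (20-40%) and residual effect (1-2 NPRS points), a gap of 10-15 points shifts the pain difference by about 0.1-0.3 points, at most about half of a 0.60 standard error. Gaps of at least 10 points would arise in about 21-30% of trials. None of this invalidates the planned analysis.

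Three stronger readings are not supported:
- **That the treatment estimate is biased.** The shift is conditional on the realised imbalance and averages to zero over repeated trials.
- **That eligibility spans mild conduction changes.** Taken literally, the entry condition shuts out the minimal grade, so the range may be only moderate to severe.
- **That results within each class could check an overall finding of similarity.** If 30% of 50 per arm fall in one class (assumed), that is 15 per arm. The standard error is 3.0 x sqrt(2/15) = 1.1 and the 95% interval is about +/-2.1 to 2.2 points, wider than the 2.0-point target. A main effect for class would not reveal differing treatment effects either.

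**What to change.** In the Protocol's Statistical Analysis section, pre-specify the electrodiagnostic severity class, as recorded at entry, as a fixed factor in the primary ANCOVA beside the baseline outcome. Reconcile the entry condition with the three-grade scheme. If the minimal class is then empty, the factor is moderate versus severe.

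The cost is one degree of freedom with two classes or two with three. No extra patients, visits or data are needed. The allocation list can stay as it is: the cards are already prepared, and discarding them for a gain of this size is not warranted.
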